## Abstract

*Background and Objectives:* The focus on mild cognitive dysfunction in adults is of great interest, given the risk of worsening and conversion to dementia. Cognitive dysfunctions are characterized by a decrease in the weight and volume of the brain, due to cortical atrophy, with a widening of the grooves and flattening of the convolutions. Brain atrophy that mainly involves the hippocampus is related to the progression of cognitive impairment and the conversion from mild cognitive dysfunction to dementia. Currently, there is no treatment for MCI. Results from a trial on Alzheimer’s disease (ASCOMALVA trial) suggest that a sustained cholinergic challenge can slow the progression of brain atrophy typical of Alzheimer’s disease associated with vascular damage. This study intends to evaluate the efficacy of choline alphoscerate in patients with mild cognitive impairment (MCI) and associated vascular damage, in stabilizing and/or slowing brain atrophy typical of adult-onset cognitive dysfunction, and in improving and/or slowing the progression of cognitive and behavioral symptoms associated with MCI. *Materials and Methods*: This randomized controlled trial will recruit 60 patients that will be evaluated and randomized in a 1:1 ratio to receive choline alphoscerate (1200 mg/day) or placebo, for 12 months. Analyses will be carried out using SPSS vesion No 26 the Statistician in charge of this study, with the statistical significance level chosen as 0.05. *Discussion*: This trial may provide evidence about the efficacy of treatment with the cholinergic precursor choline alphoscerate in patients with mild cognitive dysfunction. The results of this study will be published in peer-reviewed journals. *Registration***:** EudraCT number: 2020-000576-38

## 1. Introduction

### Background

In recent years, attention to cognitive dysfunctions has increased. Given that Alzheimer’s disease (AD), and dementia in general, remains one of the most relevant problems for public health today, there is growing attention, on the part of both social and health systems, of tools and strategies to recognize the cognitive decline, and possibly distinguish “mild cognitive dysfunction” from “dementia” [1]. The focus on mild cognitive dysfunction in adults is of great interest, given the risk of worsening and conversion into overt dementia [2,3].

Mild cognitive impairment (MCI) is a clinical condition characterized by a difficulty in one or more cognitive domains, such as, memory, attention, or motivation, identified through neuropsychological tests, but not compromising the normal and daily activities of the patient [4].

There is currently no approved drug treatment for mild cognitive dysfunction defined by the current criteria that include evidence of objective cognitive impairment (typically memory), the preservation of general cognitive and functional abilities, and the absence of diagnosis of dementia [5]. Many of the drugs approved for the treatment of AD have been evaluated as potential therapies for the treatment of cognitive dysfunction without dementia. Systematic reviews and meta-analyses evaluating the efficacy of cholinesterase inhibitors (ChE-Is) for the treatment of cognitive impairment without dementia concluded that there is no convincing evidence that this class of compounds is effective on cognitive abilities [6,7,8]. A review that evaluated the effects of donepezil, rivastigmine, galantamine, or memantine on mild cognitive impairment concluded the ineffectiveness of all these drugs [6]. Vitamin E and donepezil did not show efficacy after three years of treatment [9], although donepezil may have reduced the likelihood of conversion in the first twelve months of treatment. Rivastigmine, galantamine, and many other drug categories did not show benefits [10,11,12]. Collectively, available evidence indicates that ChE-Is do not affect the conversion of MCI into dementia, or if effective, they display a very mild activity [13].

Furthermore, one of the main problems of ChE-I therapy is the decrease in the effectiveness of the treatment over time [14]. Another problem is that for particular categories of patients (very elderly subjects, that is, more than 85 years old, or patients with bradycardia, bronchial asthma, or chronic obstructive pulmonary disease), the use of ChE-I is not indicated. On the other hand, high doses of ChE-I are potentially associated with important side-effects [15].

Cholinergic precursors were among the first compounds used to treat AD [16].

The efficacy of increasing the level of acetylcholine in adult cognitive impairment is reported in various studies. The data supporting the drug’s activity are reported below in several review articles and meta-analyses [16,17].

Choline alphoscerate has no particular contraindications; the only one is hypersensitivity to the product. As a precursor of biological constituents, choline alphoscerate, even for prolonged administration, generally does not pose problems of tolerability. Studies on cognitive impairment, Alzheimer’s, dementia [18], Parkinson’s [19], or Cerebral Small Vessel Disease [20] showed that the incidence of side-effects in the group treated with choline alphoscerate is low and similar to those observed in the placebo group. The possible occurrence of nausea (probably attributable to a secondary dopaminergic activation) could require a reduction in the dosage and/or suspension of the drug.

Choline alphoscerate is, among the clinically tested cholinergic precursors, the compound that has shown the greatest efficacy, as well as good tolerability in patients with mild- and moderate-phase AD and with associated vascular damage [16]. Since choline alphoscerate crosses the blood–brain barrier easily, it likely acts as an active choline donor in the brain and has been shown to exert neuroprotective effects in experimental animals with vascular brain injury. Based on these considerations, a study called ASCOMALVA (association between the cholinesterase inhibitor donepezil and the cholinergic precursor choline alphoscerate in Alzheimer’s disease with cerebrovascular injury) recruited patients with AD associated with vascular damage, a patient population characterized by marked cholinergic hypofunction [21,22]. This study has shown that the group of patients treated with donepezil alone (control group) was more impaired on cognitive tests: the Mini-Mental State Examination (MMSE) and Alzheimer’s Disease Assessment Scale—Cognitive Subscale.

(ADAS-Cog) scores, functional scores, and the Instrumental Activities of Daily Living (IADL) were compared to the group treated with the combination choline alphoscerate and donepezil (experimental group) [18]. Moreover, the ASCOMALVA study has shown a greater benefit of the association of donepezil plus choline alphoscerate versus donepezil alone on behavioral disorders [23], particularly on apathy [24], with a significant reduction in the stress of the caregiver. Within the ASCOMALVA study, the difference in the brain volume of the two treatment groups was evaluated with the analysis of 3-year Magnetic Resonance Imaging (MRI) using voxel morphometry techniques. Results of this study have shown that the rate of atrophy progression was significantly higher in the group that received only donepezil than in the group that received the combination choline alphoscerate and donepezil (experimental group). The reduction in atrophy in the hippocampal and amygdaloid areas is consistent with the clinical efficacy demonstrated in terms of the reduction in cognitive loss (MMSE and ADAS-Cog scores) [18]. These results suggest that the marked cholinergic challenge induced by treatment with cholinergic precursors ChE-I + choline alphoscerate can slow the progression of brain atrophy typical of AD associated with vascular damage. Based on these results, this study aims to evaluate the effectiveness of the cholinergic precursor, choline alphoscerate, in subjects with mild cognitive dysfunctions with associated vascular damage.

## 2. Methods

### 2.1. Objectives of Study

#### 2.1.1. Primary Objective

This study intends to evaluate the slowing and/or stabilization of atrophy of the hippocampus, entorhinal cortex, neocortex, and ventricular dilation induced by treatment with the cholinergic precursor choline alphoscerate in patients with mild cognitive dysfunction with associated vascular damage.

#### 2.1.2. Secondary Objectives

This study intends to evaluate whether the effectiveness of the cholinergic precursor choline alphoscerate is superior to that of placebo in the stability and/or improvement in cognitive abilities.

Functional performances and changes in mood and motivation will also be monitored. The safety and tolerability of the study drug will be evaluated.

#### 2.1.3. Primary Endpoint

The volume (mm^3^) of the hippocampus, entorhinal cortex and neocortex and the dilation of lateral ventricles determined from T1-weighted MRI will be analyzed at 12-month intervals. Treatment will be deemed successful if atrophy of the areas is significantly lower than that of the control group at 12 months. Cognitive impairment will be measured using the MMSE scale at the final visit compared to baseline, and treatment will be successful if MMSE is significantly higher than that of the control group at 12 months

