#### 2.1.4. Secondary Endpoints

Cognitive abilities will be assessed through the use of neuropsychological scales that evaluate the cognitive performance of patients (executive, memory, visual-constructive, linguistic, and attentional functions) at 6 months and at end of this study compared to the baseline visit. Treatment will be successful if cognitive performances are significantly higher than those of the control group at 12 months. Functional performances and changes in mood and motivation will be evaluated with specific neuropsychological tests, and treatment will be successful if functional performances are significantly higher and behavioral impairment significantly lower than those of the control group at 12 months.

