### 4.2. Methods

All the variables will be descriptively analyzed by treatment and visit (mean, median, standard deviation, interquartile range for continuous variables, frequency distribution for categorical variables). Efficacy analysis will be applied in all populations. Results from the ITT (Intention To Treat) population will be considered the primary ones.

Analyses will be performed using SPSS by the Statistician in charge of this study (different from the above-mentioned Independent Statistician). The statistical significance level chosen is equal to 0.05.

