### 4.3. Analysis

The treatment comparison on the difference between the two arms in the changes in brain hippocampal volume at the final visit from baseline will be performed using Repeated-Measures ANOVA.

The test will be conducted at the standard 0.05 significance level. In case of a non-normal distribution, the data will be normalized through a log-transformation. A non-parametric method will be used in case the normality will not be observed after the data transformation.

The treatment effect will be estimated in terms of the difference in changes at the final visit from the baseline between the two treatments, and the corresponding two-sided 95% Confidence Interval (CI) will be provided. All the secondary endpoints will be analyzed according to their standard methods. All the statistical methods will be detailed on the Statistical Analysis Plan which will be finalized before the database freezing. Statistical analysis of the safety data will address the safety population. No method for replacing missing values will be applied, and all the missing datapoints will be removed from analysis according to pairwise exclusion. The MedDRA dictionary will be used for coding AEs. AEs will be summarized by the System Organ Class (SOC) and Primary Preferred Term (PPT). They will also be stratified by seriousness and relationship with the study treatment. All abnormalities noted on the physical examination at enrolment and during this study will be descriptively analyzed as the frequency distribution. Previous and concomitant medications will be coded using the WHO dictionary with the ATC codes. Concomitant diseases at study entry will be coded with the MedDRA dictionary. These data will be descriptively analyzed as frequency distributions.

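### The protocol contradicts itself on what is primary (five, four or one measure), so the 5% error and 95% power are not fixed for its success rule

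*Protocol article*

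**What the plan says.** Five sections of the protocol article bear on what is primary, and they do not agree.

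- **Section 2.1.3 (Primary Endpoint)** lists "The volume (mm^3^) of the hippocampus, entorhinal cortex and neocortex and the dilation of lateral ventricles determined from T1-weighted MRI". Its first success rule is "Treatment will be deemed successful if atrophy of the areas is significantly lower than that of the control group at 12 months". A second rule follows for cognition: "treatment will be successful if MMSE is significantly higher than that of the control group at 12 months".
- **Section 2.1.1 (Primary Objective)** concerns "atrophy of the hippocampus, entorhinal cortex, neocortex, and ventricular dilation induced by treatment". MMSE is not mentioned.
- **Section 2.1.2 (Secondary Objectives)** places cognition there, asking whether the drug is "superior to that of placebo in the stability and/or improvement in cognitive abilities".
- **Section 4.1 (Sample Size)** bases the calculation on hippocampal volume (difference 0.7 cm³, SD 0.6, two-sided 0.05, power 95%) and arrives at 42 patients. It then describes that number as enough to detect two MMSE points.
- **Section 4.3 (Analysis)** names one treatment comparison, on "changes in brain hippocampal volume at the final visit from baseline will be performed using Repeated-Measures ANOVA".

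On the significance level, section 4.2 says "The statistical significance level chosen is equal to 0.05", and section 4.3 repeats 0.05. No split or order of testing is given.

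**The concern.** The primary set is five measures in section 2.1.3, four in section 2.1.1 and one in sections 4.1 and 4.3. Within section 2.1.3 two logical links are missing. The first is whether one area is enough or all four are needed. The second is whether the MMSE rule is joined to the MRI rule by *and* or by *or*.

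These links determine the trial's operating characteristics. A rule met by any one of several tests raises the chance of a false success. A rule that needs several tests at once lowers power. The protocol's figures of 5% and 95% describe neither; they describe one test on the hippocampus. As the text stands, a lone MMSE or entorhinal result could be reported as meeting the primary endpoint, and so could a hippocampal result on its own. Each claim could cite a section in support.

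**Working it through.** **Step 1. Reproduce the plan's own figure.** Inputs from section 4.1: difference 0.7 cm³, SD 0.6, two-sided α = 0.05, power 95%.

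- Normal approximation: n per arm = 2 × (1.96 + 1.645)² × (0.6/0.7)² = 19.1, so 20.
- Exact two-sided t test: 20.1, so 21 per arm and 42 in total, as stated. Power at 21 per arm is 95.8%.
- With a difference of 2 and SD 0.6, the t test needs only 3.6, so 4 per arm. The 42 is therefore a hippocampal figure. No SD for MMSE is given, so MMSE has no power basis in the document.

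**Step 2. Any one of the five measures suffices, each tested at two-sided 0.05.**

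- Independent tests: 1 − 0.95⁵ = 22.6%.
- Counting only results in favour of treatment: 1 − 0.975⁵ = 11.9%, against a nominal 2.5%.
- The documents give no correlations, so I assume equicorrelated normal test statistics:

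| Correlation | At least one significant, either direction | At least one in favour of treatment |
|---|---|---|
| 0 | 22.6% | 11.9% |
| 0.3 | 21% | 10.5% |
| 0.5 | 18% | 9.2% |
| 0.7 | 15% | 7.4% |

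**Step 3. All four areas, or else MMSE.**

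- With no effect on anything and independent tests, the favourable error is 1 − (1 − 0.025⁴)(1 − 0.025) = 2.5%. At correlation 0.7 it is 2.6%.
- Suppose three areas truly respond and are almost sure to be significant, while the fourth area and MMSE do not respond. Two null tests then each offer a route to success: 1 − 0.975² = 4.9%.

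**Step 4. All five measures required.**

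- The favourable error with no effect on anything stays below 0.3% for correlations up to 0.7.
- If each test has 95% power (an assumption for the four measures other than the hippocampus), joint power is 0.95⁵ = 77% if independent and about 87% at correlation 0.7.
- If every measure had the hippocampal standardised effect at 21 per arm, independence gives 0.958⁵ = 81%.

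**Step 5. Hippocampus only, as in sections 4.1 and 4.3.** Error is 5% two-sided, power is 95.8%, and 42 evaluable patients stands.

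Only step 5 yields both of the protocol's figures, and it is not what section 2.1.3 says.

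**The case against.** **The error may well be nominal.** The first success rule speaks of the areas collectively and does not say that one of them is enough. Read as all four areas, with MMSE as a second route, the favourable error is about 2.5% with no effect anywhere (step 3). This stands. A reader might infer that the trial's error rate is inflated as a matter of fact; the documents do not support that. Inflation follows only from the any-measure reading. The 22.6% figure also assumes independence and counts results favouring placebo, which section 2.1.3 does not call success.

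**The analysis plan can settle it in time.** Section 4.3 says the methods will be detailed in a statistical analysis plan finalised before the database freeze. The Randomization section keeps the investigator, data managers and analysts blinded until database lock. A reader might infer that the verdict could be picked after unblinded results are seen; these safeguards, if kept, prevent that. They do not remove the conflict. The protocol has already stated two success rules that its own objectives, sample size and analysis do not match, and an analysis plan following any one section would contradict another.

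**The secondary endpoints.** A reader might extend the charge to section 2.1.4, which says "Treatment will be successful if cognitive performances are significantly higher than those of the control group at 12 months". That section gives no count of tests, section 4.3 leaves the secondary methods to standard practice and the analysis plan, and unadjusted secondary endpoints are common. It is not part of this point.

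**Conclusion.** The contradiction is real and lies in the protocol text itself. It is not a missing multiplicity detail. The exact conclusion is that the 5% error and 95% power are *not fixed* for the success rule as written:

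- any of five: about 15–23% two-sided, or 7–12% in favour of treatment against 2.5%;
- all four areas, or MMSE: about 2.5% in favour of treatment with no effect anywhere, rising to about 5% if only some areas respond;
- all five: error controlled, joint power about 77–87%;
- hippocampus alone: 5% and 95%, as stated.

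The ranges rest on assumed correlations of 0 to 0.7. The joint-power figures also assume 95% power for each measure, for which the document offers no support outside the hippocampus. Because the fault concerns the definition of trial success, it should be corrected before the analysis plan is finalised. Whether 0.7 cm³ is a sound target for a 12-month change is a separate question, not judged here.

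**What to change.** **Preferred.**

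- In section 2.1.3, name the between-arm difference in 12-month change in hippocampal volume as the single primary endpoint.
- Move entorhinal cortex, neocortex, lateral ventricles and MMSE to key secondary endpoints, tested in a fixed sequence or by Holm only if the primary succeeds.
- Align the primary objective in section 2.1.1 with this.
- In section 4.1, replace the two-point MMSE difference with the hippocampal difference actually used (0.7 cm³, SD 0.6).

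The cost is wording in the protocol and the analysis plan. The level stays 0.05, 42 evaluable patients stands, and no new data are needed. The downside is that a lone MMSE or entorhinal result can no longer be claimed as primary success.

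**Alternative, closer to section 2.1.1.** Keep the four MRI measures as co-primary with an explicit rule that all must be significant, make MMSE secondary, correct the MMSE sentence in section 4.1, and restate the power for the joint rule. With 95% per test and independence, joint power is 0.95⁴ = 81%; positive correlation raises it. Restoring 95% jointly needs 0.95^(1/4) = 98.7% per test. At the hippocampal effect size that is 27 per arm, or 54 evaluable. The planned 60 would supply 54 only if losses stayed at or below (60 − 54)/60 = 10%.

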#### 2.1.4. Secondary Endpoints

Cognitive abilities will be assessed through the use of neuropsychological scales that evaluate the cognitive performance of patients (executive, memory, visual-constructive, linguistic, and attentional functions) at 6 months and at end of this study compared to the baseline visit. Treatment will be successful if cognitive performances are significantly higher than those of the control group at 12 months. Functional performances and changes in mood and motivation will be evaluated with specific neuropsychological tests, and treatment will be successful if functional performances are significantly higher and behavioral impairment significantly lower than those of the control group at 12 months.

#### 2.1.5. Safety Endpoint

The safety and tolerability of the study drug will be evaluated through the detection of adverse events (AEs), laboratory parameters, vital signs, and physical examination throughout the course of this study.

### 2.2. Study Population

A total of 60 patients, with mild cognitive dysfunction, meeting the following selection criteria will receive the study drug/placebo.

#### 2.2.1. Inclusion Criteria

These include the patient being able to understand and sign the informed consent or the informed consent being signed by a family member/caregiver.

Age ≥ 65 years.Memory disorder presence evaluated by neuropsychological testing.MMSE: score ≥ 24.Clinical Dementia Rating (CDR) = 0.5.Sufficient education to enable the patient to read, write, and communicate effectively.Independent patient in daily, family, work, and/or social activities.Cooperative patient and able to complete all aspects of this study alone or with the help of a family member.Patient living with or in contact with a family member/caregiver who cooperates in the efficacy evaluation.MRI performed within 6 (six) months prior to enrolment.Presence of at least 2 (two) vascular risk factors including systemic arterial hypertension; diabetes mellitus; obesity; heart disease (e.g., atrial fibrillation); dyslipidemia; hyperhomocysteinemia; tobacco addiction; previous cerebrovascular events; and family history of cardio-cerebrovascular diseases.

#### 2.2.2. Exclusion Criteria

MMSE: score < 23.Clinical Dementia Rating (CDR) > 0.5.All decompensated cardiac disorders.Chronic renal failure.Severe hepatic insufficiencyIncorrect dysthyroidism (level T3 different from 1.1–2.6 nmol/L, T4 different from 60–150 nmol/L).Serious ongoing developmental systemic pathologies (e.g., malignancies).Any advanced, progressive, or unstable disease that, in the opinion of the investigator, could interfere with efficacy or safety assessments or that could put the patient at risk by participation in the study.Psychiatric disorders or intellectual disability (psychosis, dissociative syndrome).Alcohol/drug/substance abuse or dependence.Diagnosis of major depression according to DSM V tr (Diagnostic and Statistical Manual of Mental Disorders Text Revision), except in cases successfully treated with a stable dose of an antidepressant (non-anticholinergic) for at least 4 weeks prior to recruitment.Any contraindication to treatment or intolerance to choline alphoscerate.Patient involved in other clinical trials.

